## Abstract

**Background:**

Problematic alcohol consumption is associated with a high disease burden for affected individuals and has a detrimental impact on companies and society due to direct and indirect health costs. This protocol describes a study design to evaluate the (cost)-effectiveness of a guided and unguided Internet-based self-help intervention for employees called “GET.ON Clever weniger trinken” (be smart – drink less) compared to a waiting list control group.

**Methods:**

In a three-arm randomized controlled trial, 528 German adults who are currently members of the workforce will be recruited by occupational health departments of major health insurance companies. Employees aged 18 and older displaying problematic drinking patterns (>21/14 drinks per week and an AUDIT score > 8/6 for men/women) will be randomly assigned to one of three following study conditions: 1. unguided web-based self-help for problematic drinking, 2. adherence-focused guided self-help, and 3. waiting list control. Self-report data will be collected at baseline (T1), 6 weeks (T2), and 6 months (T3) after randomization. The primary outcome will be the reduction of alcohol standard units during the 7 days prior to T2, using the Timeline Followback method. Cost-effectiveness analyses to determine direct and indirect costs will be conducted from the perspectives of employers and the society. Data will be analyzed on an intention-to-treat basis and per protocol.

**Discussion:**

There is a need to identify effective low-threshold solutions to improve ill-health and reduce the negative economic consequences due to problematic alcohol drinking in workforces. If the proposed web-based intervention proves both to be efficacious and cost-effective, it may be a useful tool to increase utilization rates of interventions for problematic drinking in occupational settings.

**Trial Registration:**

German Register of Clinical Studies (DRKS): DRKS00006105, date of registration: 2014-07-07.

## Background

### Problematic alcohol use - a global health problem

Problematic alcohol consumption is associated with a high burden of disease [1, 2]. Alcohol use disorders (AUDs) are projected to become the fourth leading cause of disability in high-income countries by 2030 [3]. The 12-month prevalence for alcohol dependence in the U.S. population is estimated to be 7 % [4] and in the German population 3.4 % [5]. AUDs are also linked to mental health problem domains, such as mood and anxiety disorders [6], work stress [7] and are associated with an increased risk for premature mortality [8].

However, the proportion of people with problematic drinking patterns that exceed the low-risk threshold but do not result in an AUD is even higher and might be more suitable to illustrate the actual dimension of the health problem [9]. Prevalence rates of such patterns vary considerably because there is no consensus when problematic drinking begins [10, 11]. For example, in 2013, 24.6 % of the U.S. population reported binge drinking, i.e., having five or more drinks in one occasion within the last month [4]. In the German population, 14.2 % of men and women drink more than 24 and 12 g of alcohol per day, respectively [5], and 33.6 % engage in hazardous drinking as defined by the short form Alcohol Use Disorders Identification Test [12].

In the present study, problematic drinking is alcohol consumption that is likely to lead to physical or psychosocial harm and will be defined based on the recommendations of the World Health Organization [13]. According to this, people engaging in problematic drinking consume more than 14 (women) or 21 (men) standard units of alcohol per week. Problematic alcohol consumption is associated with considerable costs due to impaired productivity and absence from work [14, 15]. Total alcohol-attributable costs per person range between $358 and $837 in high-income countries [2]. Indirect costs such as those due to productivity losses have shown to be the predominant cost-category with an average 72.1 % of all alcohol-attributable costs in high-income countries [2].

There are good reasons for offering services that help to reduce alcohol consumption in occupational settings. Workplaces offer a high potential for delivering alcohol prevention by reaching a high proportion of the target group [16, 17]. As there are correlations between alcohol drinking, absence from work, and related costs [18], occupational prevention programs may help to reduce impaired productivity due to, for example, alcohol-related absenteeism and presenteeism [19]. Moreover, Siegrist and Roedel [20] found evidence from prospective studies that work-related stress is a risk factor for problematic alcohol consumption. Based on a social learning paradigm, people may use alcohol as an alternative mechanism to cope with stressful situations (e.g. work stress) [21]. Such situations may include difficulties to relax from work or to cope with negative emotions. According to social environment models, peer pressure and the omnipresent availability of alcohol may add to the risk of increase drinking in those situations. Reducing these risk factors by providing exercises of emotional coping as a major part of an intervention might be beneficial.

### Existing treatments at the workplace

Different approaches have been tested in occupational settings, for example, education programs, personal counseling, individual feedback, brief mail-out interventions, and management training [22]. However, effects of these interventions are mixed, and many studies lack sufficient methodological quality [22, 23]. Traditional occupational interventions are typically offered in large businesses that have an employee assistance program or other health-promoting plans. Thus, especially people in smaller businesses are less likely to have access to these kinds of prevention programs [16]. Another barrier for implementing health interventions at the workplace may be low participation rates [23]. Reasons for these low rates include a preference for self-helping attempts [24] and a fear of stigmatization [25, 26].

### Potential of web-based interventions

Using the Internet to provide brief self-help interventions may help to overcome some of the barriers for implementing traditional occupational health programs. People can access the intervention at any time and at any place without disclosing their identity [16]. Other advantages include the fact that participants can work at their own pace and review materials as often as they want. In addition, such interventions possibly reach affected people earlier than traditional health services, thereby preventing the onset of more severe health problems [27].

### Efficacy of web-based interventions for problematic alcohol use

In recent years, studies on web-based interventions for alcohol reduction have been on the rise [28, 29]. Meta-analyses have revealed effect sizes of these kinds of interventions for reducing weekly alcohol units ranging from g = 0.2 [28] to d = 0.4 [29].

### Web-based occupational health interventions for problematic alcohol use

There have only been a few studies on web-based alcohol interventions in occupational settings. For example, employees from an U.S. technology company participated in a web-based health promotion program designed for universal prevention of depression, anxiety, and problematic substance use [30]. This study showed that employees participating in this program were slightly more willing to change their drinking behavior compared to those in the control group. However, data of the total amount of drinking was not reported. Doumas and Hannah [31] tested a brief website that provides personalized normative feedback (PNF) on drinking to young employees in the 18-24-year age group. The study group found small effects on reductions of weekend drinking (d = 0.3), peak consumption (d = 0.3), and intoxication (d = 0.2) compared to a control group. Pemberton and his co-authors [32] tested a brief web-based intervention for high-risk drinkers and a web-based universal prevention program including PNF, motivational interviewing elements, and skills for behavioral change in military personnel. They found small effects for the intervention for high-risk drinkers on average drinks per drinking occasion, frequent heavy episodic drinking status, and estimated peak blood alcohol concentration (all about d = 0.1 compared to a control group). In contrast, the effects of the prevention program were not significant. In a more recent study, Khadjesari and colleagues [33] analyzed the effects of an online screening and PNF in a workforce in the UK, but did not find improvements with regard to drinking behavior. In the long term, after 6 months, none of these interventions showed significant effects.

However, all described interventions were tested in very specific populations, for example, military personnel [32], adolescents [31], individual companies [33], thus, it is questionable, if findings can be generalized to other workforce populations. Moreover, to the best of our knowledge, none of these studies included an economic evaluation. All of the interventions mentioned above are based on a self-help paradigm. However, unguided web-based interventions, that means those without any human support (i.e., pure self-help), have been found to be less effective than guided interventions for depression and social phobia [34]. With regard to interventions for problematic alcohol consumption, the picture is less clear. In a recent meta-analysis, Riper and her co-authors [28] did not find differences in terms of efficacy between guided and unguided interventions across different studies, but the number of trials with guidance was very small (*n* = 5). Thus, there is a need to explore the (cost-)effectiveness of web-based interventions for reducing problematic alcohol consumption with and without guidance in the same study.

## Aims of the study

The scope of this study is to evaluate the (cost-)effectiveness of a newly developed web-based cognitive-behavioral self-help intervention called GET.ON Clever weniger trinken (CWT) for employees with problematic alcohol consumption. The study has the following aims: 1) to assess the effectiveness of self-help CWT for reducing alcohol consumption compared to a control group, 2) to assess the effectiveness of CWT with adherence-focused guidance compared to a control group, 3) to assess the incremental cost-effectiveness ratio (ICER), that is the ratio between costs and clinical outcome, of guided and unguided CWT compared to a control group. We expect both intervention groups to be superior compared to the control group in terms of alcohol consumption reduction from baseline to the post-assessment. We hypothesize guided and unguided self-help CWT both to be more cost-effective compared to the control group at the 6-month follow-up assessment. As a secondary aim we explore the differences of additional professional support, i.e., adherence-focused guidance [35].

## Methods

### Study design

A three-arm randomized controlled trial (RCT) will be conducted to evaluate the web-based intervention CWT with and without guidance compared to a waiting list control group (WLC). Assessments will take place before the allocation to the study conditions (T1), 6 weeks (T2), and 6 months (T3) after the allocation (Fig. 1). All procedures involved in the study will be consistent with the generally accepted standards of ethical practice approved by the University of Lueneburg (Germany) ethics committee (No. [name]201404_OT). The trial is registered in the German clinical trials register DRKS00006105.

**Fig. 1 Fig1:**
[figure not shown]
Study flow

### Participants & procedure

#### Inclusion and exclusion criteria

We include (a) working people, (b) who are above the age of 18, (c) who report drinking of at least 14/21 (women/men) standard units per week, (d) who have a score of at least 6/8 for women/men on the Alcohol Use Disorders Identification Test (AUDIT) [36], (e) who have Internet access, (f) who have sufficient German language reading and writing skills (self-reported), and (g) who are willing to give informed consent. We exclude subjects (a) who indicate that they have been diagnosed with psychosis or a drug dependency in the past, (b) who show a notable suicidal risk as indicated by a score greater than 1 on BDI [37] Item 9 (“I feel I would be better off dead”), (c) who have received medication or have begun psychotherapy to treat their problematic alcohol consumption, and (d) who are participating in another study on online-health training of our study group at the same time.

#### Recruitment

Participants will be recruited nationwide from the German-speaking population. The recruitment process is scheduled from autumn 2014 to autumn 2015 and will be conducted by several health insurance companies (BARMER GEK, KKH, BKK). The insurance companies advertise the study in their member-journals that will be sent to all of their insurants and they promote the study participation on their websites. Nevertheless, participation is not limited to the insurants of these companies and is not restricted to specific industrial sectors or occupational groups. An open access website (http://www.geton-training.de/alkohol) provides information on the intervention and study conditions. Potential participants sign up by providing an email address and name or pseudonym on the website.

#### Assessment of eligibility and randomization

The trial will be open to all people who meet criteria listed above. After registering, applicants receive an email with detailed information about the study procedures. Then, they will be informed that they can withdraw from the intervention and/or study at any time without any negative consequences. Applicants who continue to participate in the study will be asked to complete an online screening questionnaire. They must fulfill all criteria of inclusion and none of the exclusion criteria, have to complete the baseline assessment (T1), and return the informed consent form to participate in the study.

Eligible applicants will be randomly allocated in a 1/1/1 ratio to one of the three trial arms: adherence-focused guided CWT, unguided CWT, or WLC. Randomization will take place at an individual level. The allocation will be performed by an independent researcher not otherwise involved in the study, using an automated computer-based random integer generator (randomisation.eu). During the randomization process, allocation will be concealed from participants, researchers involved in recruitment, and eCoaches. After being informed about the outcome of the randomization, participants in the two intervention groups will receive immediate access to the training. All data is collected using a secure web-based assessment system (AES, 256-bit encrypted).

### Intervention

The web-based intervention CWT comprises five modules (Table 1). Each includes general information, illustrative examples, interactive exercises, quizzes, audio and video files, and downloadable work sheets (Figs. 2, 3, 4). The intervention combines different examples of good clinical practice in alcohol treatment [38], tools to control drinking behavior [39], and an emotion regulation training [40]. The combination of these elements is meant to initiate and promote the processes of change that allow participants to move from one stage of behavioral change to another, as defined by the Transtheoretical Model of Health Behavior Change [41].

**Table 1 Tab1:** Content of the web-based training GET.ON CWT

Module	Intervention content
1	Psychoeducation
	Personalized normative feedback
	Motivational interviewing
2	Planning of behavioral change
3	Maintenance of behavioral change
	Emotion regulation
	Behavioral activation
4	Maintenance of behavioral change
	Emotion regulation
5	Planning for the future

**Fig. 2 Fig2:**
[figure not shown]
Video that introduces training goals

**Fig. 3 Fig3:**
[figure not shown]
Example of adaptive content

**Fig. 4 Fig4:**
[figure not shown]
Example of a writing exercise for behavioral change planning

Participants are advised to complete each module within one week. The Module 1 includes three major sections: section a) provides an overview of the training content, an explanatory model of conditions that may lead to increased consumption of alcohol (e.g. the wish to relax after work or some kind of peer pressure), and an explanation of alcohol standard units and why this measure is useful to monitor alcohol consumption. Section b) consists of personalized normative feedback. By completing a short self-assessment, participants identify their own drinking patterns in comparison to normative drinking guidelines. Participants who show a drinking pattern of high risk for alcohol dependency receive information about health services they should use in addition to the online intervention. Participants belonging to a high-risk group (e.g. pregnant participants) are advised to abstain from alcohol. This kind of a normative feedback element as stand-alone-intervention has been shown to effectively reduce drinking [42]. It aims to enable participants to reconsider their drinking habits by comparing their own alcohol consumption to that of peers and health norms [43]. In section c) different exercises are presented in a non-directive style based on motivational interviewing principles [44] that are meant to elicit behavioral change. The participants reflect on advantages and disadvantages of their drinking, think of reasons for change, and determine a personal goal (e.g. to reduce alcohol consumption in specific situations, to become abstinent, or to just monitor drinking habits).

An additional tool of the training program is an online-diary, which participants can use to record how much they drank on the previous day and to set a personal limit for the next day. At the beginning of each subsequent module, participants reflect on their drinking on the previous days. The diary is accessible via Internet or smartphone.

The core element in Module 2 is a four-step plan to control alcohol consumption in specific situations. It is theoretically based on the Health Action Process Approach (HAPA) [45] and elements of the Problem Solving Therapy (PST) [46]. The plan consists of the following steps: 1) Participants choose a typical situation in which it is hard for them to abstain from alcohol, 2) determine a drinking limit for this situation, 3) explore possible solutions for behavioral change in this kind of situation, and 4) describe in detail how to put their solution into practice. At the end of Modules 2 to 5, participants receive additional information and techniques they can use to achieve their goals. This optional toolbox contains information on the following topics: how to refuse alcohol in social contexts, how to control situations in which alcohol is easily available (stimulus control), how to change drinking habits, and how to relax after work without drinking (relaxation techniques).

In Module 3, participants reflect on their first efforts of controlling alcohol, adopt or adapt a plan for behavioral change, or develop a new plan in response to another problematic drinking situation. Participants are then introduced to the nature of different emotions and how these are linked to alcohol consumption. There is evidence for the detrimental impact of negative emotional states on maladaptive drinking [47, 48]. Furthermore, participants start to learn evoking positive emotions without using alcohol, for example, by planning enjoyable activities. This planning process can be continued throughout the other modules.

Module 4 comprises techniques of emotional regulation to cope with negative affective situations. The core exercise is to accept and tolerate negative emotional states based on the Affect Regulation Training (ART) [40, 49]. Acquiring these competencies may help individuals to improve their drinking habits [50]. Participants begin this exercise by recognizing a situation in the past when they had to struggle with their emotions. Then, they reflect on the usefulness and positive aspects of the unwanted (negative) emotions and develop strategies for coping with them in this kind of situation (i.e., by accepting the current emotional state). At the end of the exercise, they are reminded that they are able to bear the acute emotion and that this state will pass.

Finally, in Module 5, participants think of their progress and describe how they can continue to improve. They define an alcohol limit for the future and choose techniques that appeared to be useful to stay within the limit that they have set for themselves.

### Study conditions

#### Unguided CWT

Participants of the unguided intervention group will communicate with the team organizing the study during the study period but will not be supported by an eCoach. In the case of any technical problems, they can contact support via email.

#### Adherence-focused guided CWT

Participants of the guided intervention group will be supported by an eCoach. Guidance is mainly based on the supportive-accountability model of guidance in Internet interventions [51]. In this study, the primary aim of guidance will be to support participants to adhere to the training schedule. Every participant in this study group will be assigned to an eCoach during the training. The eCoaches are trained psychologists and will follow guidelines for the feedback process that are defined according to the content and structure of the intervention. At the beginning of the training, eCoachs send a message to the participants clarifying their supportive role in the program. Coaching guidance consists of two elements: a) adherence monitoring and b) feedback on demand. These principles of guidance have already been described elsewhere [35].

*Adherence monitoring* includes regularly checking whether participants have completed the intervention modules on time and sending reminders if they did not complete at least one module within 7 days. The reminders are formulated in an encouraging and motivational style to avoid reactance. In addition, all participants receive a standardized message after having completed the first module to make sure that they stick to the program.

*Feedback on demand* includes offering participants the opportunity to contact their eCoach via the internal messaging system of the training platform and to receive individual feedback whenever such a need may arise. Within 48 h, the participants will receive personalized written feedback. The time required for coaching including all reminders and feedback is estimated to be up to 1 h per participant.

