#### Waiting list control (WLC)

Participants of the WLC will not get any kind of active training intervention. But they are informed that monitoring and reflecting on their drinking behavior by completing online-assessments can be a first step toward healthier drinking habits. In addition, participants will get access to the training after the 6-month follow-up assessment.

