### Clinical evaluation

Analyses of covariance with baseline scores as covariate will be conducted to explore the effects of the interventions compared to the control group on all primary and secondary outcomes. A-priori contrasts will be defined to test the separate effects of the guided and unguided interventions compared to the control condition. For all analyses, Cohen’s d will be calculated by subtracting the average change scores from baseline to post-assessment (T1-T2) of one study group from the other one and then dividing it by the pooled standard deviations of the change scores. We will also calculate the number needed to treat (NNT) with adherence-focused guided and unguided CWT to achieve one response, i.e., complying with the low-risk guideline, compared to the control group. For all statistical analyses, significance level will be set at p < .05 for two-sided tests.

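### Guided participants are nested within eCoaches, but the stated ANCOVA treats everyone as independent; a partially nested sensitivity analysis should guard the guided-versus-control conclusion

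*Protocol article*

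**What the plan says.** All of this is in the Protocol article.

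- **Unit of randomization** (Assessment of eligibility and randomization): "Randomization will take place at an individual level", in a 1:1:1 ratio to three arms.
- **Guided arm** (Adherence-focused guided CWT): "Every participant in this study group will be assigned to an eCoach during the training". The section speaks of eCoaches in the plural. They monitor adherence, send reminders and answer requests for feedback.
- **Limits on the coaching** (same section): eCoaches "will follow guidelines for the feedback process that are defined according to the content and structure of the intervention", and "The time required for coaching including all reminders and feedback is estimated to be up to 1 h per participant".
- **Unguided arm** (Unguided CWT): these participants "will not be supported by an eCoach".
- **Control arm** (Waiting list control): "Participants of the WLC will not get any kind of active training intervention".
- **Analysis** (Clinical evaluation), for the model: "Analyses of covariance with baseline scores as covariate will be conducted to explore the effects of the interventions compared to the control group". The same section fixes the contrasts: "A-priori contrasts will be defined to test the separate effects of the guided and unguided interventions compared to the control condition".
- **Sample size** (Sample size calculation): 528 participants, for d = 0.30, 80% power and two-sided alpha .05.

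The article does not give the number of eCoaches, their caseload or an ICC.

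**The concern.** Randomization is individual, but after it one arm acquires a cluster structure: guided participants who share an eCoach may have correlated outcomes, while participants in the other two arms remain independent. Baseline adjustment cannot remove this, because any eCoach effect arises after baseline. An ANCOVA that assumes independence in every arm then understates the variance of the guided-arm mean.

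Aim 2, guided CWT versus control, rests on that contrast. The exploratory comparison of guided with unguided is affected in the same way; aim 1, unguided versus control, is not. The two main contrasts would be reported side by side at the same nominal .05 level while having different real error rates.

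**Working it through.** **Step 1: reproduce the plan's figure.** Inputs from Sample size calculation: d = 0.30 (SD = 1), power 80%, two-sided alpha .05. A two-sample t-test on independent observations (noncentral t) needs 176 per arm, with power 0.801, and 3 × 176 = 528. The plan's figure is reproduced exactly. It contains no allowance for eCoach clustering, which is consistent with the stated ANCOVA.

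**Step 2: variance with clustering in one arm.** Let k be the number of eCoaches with equal caseloads m = 176/k, and let ICC be the eCoach intraclass correlation of the baseline-adjusted outcome. Both k and ICC are assumptions.

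- Design effect in the guided arm: DE = 1 + (m − 1) × ICC
- Var(guided − control) = (1 + DE)/176, against 2/176 under independence
- True SE / independence SE: r = √((1 + DE)/2)
- Real two-sided error of the independence test: 2 × [1 − Φ(1.96/r)]
- Power at d = 0.30 with the correct SE: Φ(0.30/√((1 + DE)/176) − 1.96)

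Worked case, k = 5 and ICC = 0.02: m = 35.2; DE = 1 + 34.2 × 0.02 = 1.684; r = √(2.684/2) = 1.158; error = 2 × [1 − Φ(1.96/1.158)] = 9.1%; power = 68%.

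| eCoaches | ICC | DE | SE ratio | Real error | Power, correct SE |
|---|---|---|---|---|---|
| any | 0 | 1.00 | 1.00 | 5.0% | 80% |
| 20 | 0.01 | 1.08 | 1.02 | 5.4% | 79% |
| 10 | 0.005 | 1.08 | 1.02 | 5.5% | 79% |
| 10 | 0.01 | 1.17 | 1.04 | 6.0% | 77% |
| 10 | 0.02 | 1.33 | 1.08 | 7.0% | 74% |
| 5 | 0.01 | 1.34 | 1.08 | 7.0% | 74% |
| 20 | 0.05 | 1.39 | 1.09 | 7.3% | 73% |
| 5 | 0.02 | 1.68 | 1.16 | 9.1% | 68% |
| 10 | 0.05 | 1.83 | 1.19 | 9.9% | 66% |
| 5 | 0.05 | 2.71 | 1.36 | 15.0% | 54% |
| 3 | 0.05 | 3.88 | 1.56 | 21.0% | 44% |

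The same formulas apply to guided versus unguided, since the comparator is again an unclustered arm of 176.

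**Step 3: simulation.** A comparison of means without a baseline covariate, 20,000 runs per setting, gave rejection rates under the null of 6.1% (10 eCoaches, ICC 0.01), 9.1% (5, 0.02) and 20.8% (3, 0.05). These agree with the formula.

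**Step 4: what a corrected primary model would cost.** With a Satterthwaite approximation at ICC = 0, the guided-arm mean carries k − 1 degrees of freedom and the control mean 175, with equal variances, so df = 4/(1/(k − 1) + 1/175). For k = 3, df = 7.9, the critical t is 2.31 and power at d = 0.30 is 69%. For k = 5, df = 15.6, the critical t is 2.12 and power is 75%. With few eCoaches the correction costs power even when there is no eCoach effect.

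**The case against.** **The ICC may be close to zero.** Coaching is adherence-focused and guideline-based, personal feedback is given only on request, and contact is at most about an hour per participant. The programme itself is delivered by the website, and the Discussion concedes that this level of support may add little. This stands: the lower rows of error in the table are at least as plausible as the higher ones, and 21% needs two unfavourable assumptions at once.

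**The independence SE can be defended.** If these eCoaches are regarded as fixed, it is adequate for a conclusion about them. This also stands, as a limit on scope. But the Discussion and Conclusions look ahead to wider use and to which guidance format suits dissemination, so the intended inference goes beyond them.

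**An article condenses.** A full protocol or analysis plan may deal with eCoach effects, the number of eCoaches and how participants are assigned to them. That those details are absent here is therefore no finding. The point concerns the model that the article does state.

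**Stronger readings to avoid.** A reader might infer that the design favours the guided version. Clustering by itself does not shift the estimate; it can only raise the false-positive rate, and only if eCoaches differ. A reader might also infer that eCoach differences are mixed up with recruitment period; nothing in the document says that assignment follows calendar time or availability.

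**Conclusion.** The point holds in conditional form. Nesting in one arm is stated, the stated model has no term for it, and the reproduced sample size has no margin for it. If the ICC is above zero and eCoaches have more than one participant each, the guided-versus-control SE is too small for inference beyond these eCoaches.

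The size is unknown because both inputs are assumed. The excess error is negligible with an ICC near zero, or with many eCoaches and a low ICC. It is moderate, about 6% to 9%, for 5 to 10 eCoaches and an ICC of 0.01 to 0.02. It is serious only in the corner with few eCoaches and a high ICC.

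The sample size of 528 is correct on its own inputs. The document does not support calling the primary analysis invalid or requiring its replacement; this is a worthwhile, low-cost improvement.

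**What to change.** 1. Store the eCoach identifier for every guided participant during the trial. Without it, the analysis may be impossible later.
2. Keep the stated ANCOVA as the primary analysis.
3. Prespecify a sensitivity analysis for each contrast involving the guided arm: the same baseline-adjusted model plus an eCoach random effect in the guided arm only, with small-sample degrees of freedom. Report the number of eCoaches and the estimated eCoach variance or ICC.
4. State in advance that the aim 2 conclusion will be qualified if it does not hold in that analysis.

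The cost is one stored field and a little more analysis. With few eCoaches, the variance estimate will be imprecise and the interval in the sensitivity analysis materially wider, which is the reason for not making it the primary model.
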